# Tri-Modality therapy with I-125 brachytherapy, external beam radiation therapy, and short- or long-term hormone therapy for high-risk localized prostate cancer (TRIP): study protocol for a phase III, multicenter, randomized, controlled trial

**DOI:** 10.1186/1471-2407-12-110

**Published:** 2012-03-22

**Keywords:** Prostate cancer, Trimodality, Radiation therapy, Brachytherapy, External beam radiation therapy, Hormone therapy, Randomized controlled trial, Biochemical progression-free survival

## Abstract

**Background:**

Patients with high Gleason score, elevated prostate specific antigen (PSA) level, and advanced clinical stage are at increased risk for both local and systemic relapse. Recent data suggests higher radiation doses decrease local recurrence and may ultimately benefit biochemical, metastasis-free and disease-specific survival. No randomized data is available on the benefits of long-term hormonal therapy (HT) in these patients. A prospective study on the efficacy and safety of trimodality treatment consisting of HT, external beam radiation therapy (EBRT), and brachytherapy (BT) for high-risk prostate cancer (PCa) is strongly required.

**Methods/Design:**

This is a phase III, multicenter, randomized controlled trial (RCT) of trimodality with BT, EBRT, and HT for high-risk PCa (TRIP) that will investigate the impact of adjuvant HT following BT using iodine-125 (^125^I-BT) and supplemental EBRT with neoadjuvant and concurrent HT. Prior to the end of September 2012, a total of 340 patients with high-risk PCa will be enrolled and randomized to one of two treatment arms. These patients will be recruited from more than 41 institutions, all of which have broad experience with ^125^I-BT. Pathological slides will be centrally reviewed to confirm patient eligibility. The patients will commonly undergo 6-month HT with combined androgen blockade (CAB) before and during ^125^I-BT and supplemental EBRT. Those randomly assigned to the long-term HT group will subsequently undergo 2 years of adjuvant HT with luteinizing hormone-releasing hormone agonist. All participants will be assessed at baseline and every 3 months for the first 30 months, then every 6 months until 84 months from the beginning of CAB.

The primary endpoint is biochemical progression-free survival. Secondary endpoints are overall survival, clinical progression-free survival, disease-specific survival, salvage therapy non-adaptive interval, and adverse events.

**Discussion:**

To our knowledge, there have been no prospective studies documenting the efficacy and safety of trimodality therapy for high-risk PCa. The present RCT is expected to provide additional insight regarding the potency and limitations of the addition of 2 years of adjuvant HT to this trimodality approach, and to establish an appropriate treatment strategy for high-risk PCa.

**Trial registration:**

UMIN000003992

## Background

The majority of low-risk patients with clinically localized prostate cancer (PCa) have a high likelihood of disease-free survival regardless of the treatment option chosen [1]. In contrast, patients with high-risk PCa with high Gleason score, elevated prostate specific antigen (PSA) level, and advanced clinical stage are at greater risk for treatment failure after initial management by single treatment modalities, such as radical prostatectomy (RP), external beam radiation therapy (EBRT), or brachytherapy (BT) [2,3]. Therefore, it is extremely important to establish the most effective and safe treatment strategy for patients with high-risk PCa, preventing local recurrence and biochemical failure at an early stage during treatment. However, high-risk PCa remains a therapeutic challenge for both urologists and radiation oncologists.

As high-risk patients have locally advanced disease with the possibility of direct extension and/or local micrometastases, various combinations of each monotherapy described above have been developed to augment disease-free survival. Recently, several studies concerning radiation therapy (RT)-based trimodality treatment method with BT, EBRT, and hormonal therapy (HT) were reported [4-6]. According to the American Brachytherapy Society (ABS), BT alone is not recommended for high-risk PCa but can be used as a boost in conjunction with EBRT [7]. Thus, the combination of BT and EBRT in this multimodal treatment approach theoretically delivers an escalated dose to the prostate, including extraprostatic extension (EPE) increasing the probability of eradicating all of the local disease. With respect to HT, neoadjuvant and concurrent androgen deprivation also offers both cytoreduction and synergistic enhancement of RT in high-risk PCa; adjuvant HT may play a role in elimination of occult systemic disease and have multiple synergistic effects to radiation on local control due to induction of apoptosis [8,9].

Some previous studies demonstrated a benefit of HT used in conjunction with EBRT to treat locally advanced prostate cancer [10-12]. However, these studies, which demonstrated an advantage with the addition of HT, were done when the radiation dose may have been inadequate to control all local disease. The question therefore that has never been answered is what benefit, if any will long-term androgen deprivation have when much higher radiation doses are delivered. Although the ABS recommends HT in conjunction with BT for cytoreduction of prostate volume, there are no clear indications for using adjuvant HT in intermediate- to high-risk PCa [7]. Moreover, both neoadjuvant and adjuvant HT may significantly induce adverse events, including fatigue, diminished sexual function, and hot flushes and possible early death [13,14]. Accordingly, investigation of the best optimal duration of HT with maximization of outcome while minimizing toxicity is a logical step in the management of localized high-risk PCa, because the prolonged use of HT may result in an increase in adverse events. It is necessary to determine which patients with high-risk PCa will actually benefit from HT despite some compromises in quality of life (QOL) associated with the adverse event profile of this treatment.

As mentioned above, the optimal RT-based trimodality protocol for use in high-risk PCa remains controversial. However, there have been no prospective studies regarding the efficacy and safety of trimodality treatment with combined HT, EBRT, and BT for high-risk patients. Such prospective clinical trials are necessary. Here, we describe our study protocol for high-risk PCa, which is a phase III, multicenter, randomized controlled trial (RCT) of a trimodality treatment protocol with BT using iodine-125 (^125^I-BT), EBRT, and neo-adjuvant and concurrent HT for 6 months with or without adjuvant HT for 2 years. We also assessed whether short-term HT without adjuvant HT or long-term HT with adjuvant HT is better with regard to improved local control and biochemical cure rate in high-risk localized PCa. The final goal of this study is to establish an appropriate treatment strategy for high-risk PCa without increasing the occurrence of adverse events.

## Methods/Design

### Aim of the study

To evaluate the efficacy and safety of long-term *vs*. short-term HT in the setting of trimodality therapy with ^125^I-BT, EBRT, and HT in high-risk PCa patients.

### Study design

The present study is a phase III, multicenter, RCT of a trimodality treatment protocol with ^125^I-BT plus supplemental EBRT with short- or long-term HT for patients with untreated high-risk PCa. We will randomly assign patients with high-risk PCa who have received ^125^I-BT and supplemental EBRT plus 6 months of HT with combined androgen blockade (CAB) into two groups: one receiving no further treatment and another receiving 2 years of HT with a luteinizing hormone-releasing hormone agonist (LH-RHa) (Figure 1).

**Figure 1 F1:**
[figure not shown]
**Study design of TRIP (UMIN000003992)**.

### Additional measures

Two validated QOL questionnaires, the SF-8™, which has been translated into Japanese, and the Expanded Prostate Cancer Index Composite (EPIC), will be administered prior to hormonal therapy and at the 60 months after the beginning of CAB to comprehensively cover the various aspects of physical and psychosocial wellbeing.

### Site selection

For an institution to participate, the institution's attending physicians must:

a. Acquire certified documentation of participation in the Japanese Brachytherapy Scientific Meeting's training session for the ^125^I-BT procedures.

b. Have experience with ^125^I-BT in at least 50 patients.

c. Regularly perform ^125^I-BT procedures.

### Eligibility criteria - Inclusion criteria

Patients must:

a. Be from 40 to 79 years of age when obtaining written informed consent.

b. Have high-risk PCa with a definitive histological diagnosis by needle biopsy. In this study, high risk is defined as those cases in which where at least one of the following three conditions is satisfied: 1) PSA > 20 ng/mL prior to CAB, or 2) clinical stage of T2c or T3a, or 3) Gleason score ≥ 8 as determined by central pathological judgment.

c. Performance status of 0-1, according to the Eastern Cooperative Oncology Group.

d. Previously untreated for PCa.

e. Appropriate bone marrow, hepatic, and renal function as demonstrated in laboratory tests within two weeks prior to registration.

a) WBC ≥ 3000/μL.

b) Hemoglobin level ≥ 10.0 g/dL.

c) Platelet count ≥ 10.0 × 10^4^/μL.

d) Serum creatine level ≤ 2.0 mg/dL.

e) ALT and AST levels ≤ 100 IU/L.

f. Computed tomography (CT) and bone scan without evidence of metastases

### Eligibility criteria - Exclusion criteria

Patients are ineligible if they:

a. Have previously received surgery and/or hyperthermia for BPH.

b. Exhibit clinical stage ≥ T3b.

c. Have a second cancer that requires treatment.

d. Have collagen diseases.

e. Have poorly controlled ischemic cardiac disease.

f. Have poorly controlled hypertension (*i.e*., diastolic pressure ≥ 120 mmHg)

g. Have a severe psychiatric disorder, including schizophrenia and dementia.

h. Have poorly controlled diabetes.

i. Are using steroid drugs other than topical ointments.

j. Are using antiandrogenic therapy.

k. Are considered by a principal or clinical investigator to be inappropriate for participation in the present study for any other reason.

### Informed consent - ethics approval

The study was conducted in accordance with the Declaration of Helsinki 1975, as revised in 2000. All treatments for prostate cancer are undertaken following written informed consent, and further consent is obtained for procedures to confirm the high-risk diagnosis. This study received approval from the Foundation for Biomedical Research and Innovation, Translational Research Informatics Center (TRI) ethical review committee (approval No. 10-12, date Sep 10th, 2010) and the institutional ethics committees of the participating institutions.

### Methods of recruitment and random allocation

Recruitment of patients is supported by the tri-modality therapy with ^125^I-BT and EBRT and short- or long-term HT for High-risk Localized PCa (TRIP) Study Group. Recruiting began in October 2010, and is planned for completion by September 2012. All prostatic biopsy histological slides of newly diagnosed prostate cancer since the initiation of the study have been reviewed by central pathologists, with patient eligibility determined at the time of review. Eligible patients are randomly assigned to one of two treatment arms through the data center at the TRI. Randomization is done centrally using a minimization method to obtain good between-group balance for factors including age category (< 70/≥ 70), PSA category (≤ 20/> 20 ng/mL), Gleason score by central pathological judgment category (< 8/≥ 8), and institutions.

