### Planned statistical analyses

It has been shown that the 7-year bPFS rate ranges from 67.8% to 83% in patients with high-risk PCa who undergo combination of BT and EBRT or trimodality treatment [5,20]. Based on these two reports, the 7-year bPFS rate of the short-term HT group is estimated to be 75%. On the other hand, the 7-year bPFS rate of the long-term HT group is estimated to be 87.5% (*i.e*., hazard ratio = 0.464) based on three RCTs comparing EBRT plus long-term HT with EBRT alone [10-12]. Taken together, 153 patients for each group are needed to detect a significant difference between treatments by log-rank test with a significance level of 0.05 and a power of 80%. Given the further assumption that approximately 10% of randomized patients will not be evaluable for various reasons, the target sample size was set at 170 patients per group (340 total).

Statistical analyses will be performed on an intention-to-treat basis. Survival curves will be estimated using the Kaplan-Meier method. The log-rank test will be used to test for differences in survival curves between the two groups of patients. The hazard ratio will be estimated using the Cox proportional hazard model. The longitudinal change of QOL scores (IPSS, SF-8™, EPIC) between diagnosis and 60 months following ^125^I-BT will also be compared between groups. Patients will be evaluated for toxicity, graded according to the National Cancer Institute Common Toxicity Criteria version 4.0 (http://evs.nci.nih.gov/ftp1/CTCAE/About.html). For all patients, the incident proportion of grade 3 adverse events will be compared between groups by Fisher's exact test. All tests will be two-sided, and a *P*-value of 0.05 will be considered statistically significant. Five years after the last patient is recruited, an interim analysis will be performed and the results will be reported to the Independent Data Monitoring Committee.

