## Discussion

High-risk PCa features are associated with poor pathological outcomes after RP [3,21]. Increasing Gleason score, high PSA level, and advanced clinical stage have all been shown to be correlated with EPE, SV invasion, and positive surgical margins. Both Partin's tables and Naito's Japanese nomograms have demonstrated the increased incidence of the above-mentioned pathological findings with higher risk features [22,23]. These pathological findings have also been shown to be associated with higher rates of biochemical failure [21,24]. Explanations for these outcomes have focused on the presence of microscopic dissemination of cancer cells at initial diagnosis. For this reason, little attention has been focused on optimizing local control and more on developing new systemic approaches. The patterns of failure following standard treatment for high-risk PCa reveal a large component of local recurrence in addition to distant spread of disease [25,26].

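### Clinical stage is the one eligibility-defining risk factor missing from the minimization list, and the described bPFS analysis has no stage term: a minor gap, not a bias

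*Protocol article*

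**What the plan says.** Protocol article, *Eligibility criteria - Inclusion criteria*: a man counts as high-risk if he meets any one of "1) PSA > 20 ng/mL prior to CAB, or 2) clinical stage of T2c or T3a, or 3) Gleason score ≥ 8". *Exclusion criteria* rules out T3b and above, so stage is known for every man before entry.

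*Methods of recruitment and random allocation*: central minimization balances age (cut at 70), then "PSA category (≤ 20/> 20 ng/mL), Gleason score by central pathological judgment category (< 8/≥ 8), and institutions". PSA and Gleason are thus balanced at exactly their eligibility cut-points. Stage is not named.

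The article treats stage as prognostic. The Abstract and *Background* list it beside Gleason score and PSA as a driver of relapse or treatment failure. The *Discussion* says "Increasing Gleason score, high PSA level, and advanced clinical stage have all been shown to be correlated with EPE, SV invasion", and then links such pathology to biochemical failure, which is the primary endpoint event.

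*Planned statistical analyses*: the groups are compared by log-rank test, and "The hazard ratio will be estimated using the Cox proportional hazard model". No covariate or stratum is mentioned.

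**The concern.** By the article's own reasoning, stage has the same claim to be balanced as PSA and Gleason. Balancing those two does not stand in for it. Among men with PSA ≤ 20 and Gleason < 8, stage must be T2c or T3a, but the split between the two is free. In every other category, men at or below T2b, at T2c and at T3a are mixed without control.

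The primary comparison rests on few events, so a chance excess of worse-stage men in one arm would move the unadjusted hazard ratio somewhat. An analysis adjusted only for the minimization factors would not correct this, because stage is not one of them.

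**Working it through.** **1. The plan's own figures.** Inputs from *Planned statistical analyses*: "the 7-year bPFS rate of the short-term HT group is estimated to be 75"%, "the 7-year bPFS rate of the long-term HT group is estimated to be 87.5"%, "log-rank test with a significance level of 0.05 and a power of 80"%, and "All tests will be two-sided".
- Hazard ratio: ln(0.875)/ln(0.75) = 0.464, as stated.
- Patients per arm: the two-proportion formula gives 152. Freedman's formula gives 58.6 events, and 58.6/0.375 = 156. The stated 153 agrees with both within tolerance.
- Inflation for 10% non-evaluable: 153/0.90 = 170 per arm, as stated.
- Expected events with all 340 men followed for 7 years: 170 × 0.25 + 170 × 0.125 = 63.75, about 64.

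**2. Size of a chance imbalance.** The share p of men in the worse stage group is not given; 30-50% is assumed. With 170 per arm, SD = √(2p(1−p)/170).
- p = 0.3: √(0.42/170) = 0.050.
- p = 0.5: √(0.50/170) = 0.054.
- In simulation, a gap above 8 points in either direction occurs in 10.8-15.2% of trials. The adverse direction, an excess in the long-term arm, is half of that: about 5-8%.
- A gap above 10 points in either direction has probability 4.4% (p = 0.3) to 6.5% (p = 0.5).

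**3. Does balancing PSA and Gleason control stage indirectly?** Minimization was simulated with 340 men, 41 sites, a biased coin of 0.8, one assumed mix of entry routes and 1,500 runs per setting. With the listed factors only, the SD of the stage difference stayed at about 5 points. With stage added it fell to about 1 point, and gaps above 10 points fell from about 4-5% to none. Type I error was 4.9% without stage and 4.1% with it (Monte Carlo SE about 0.5 points). Power was 84.0% and 82.6% (SE about 1 point). Neither difference exceeds simulation noise.

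**4. Effect on the hazard ratio.** Let h be the stage hazard ratio (not given; 1.5-2 assumed) and p₁, p₀ the worse-stage shares in the long-term and short-term arms. The treatment hazard ratio is multiplied by approximately (1 + p₁(h−1))/(1 + p₀(h−1)). For a 10-point gap:

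| p | h | Factor | 0.464 becomes |
|---|---|---|---|
| 0.3 | 1.5 | 1.175/1.125 = 1.044 | 0.485 or 0.444 |
| 0.3 | 2 | 1.35/1.25 = 1.080 | 0.501 or 0.430 |
| 0.5 | 1.5 | 1.275/1.225 = 1.041 | 0.483 or 0.446 |
| 0.5 | 2 | 1.55/1.45 = 1.069 | 0.496 or 0.434 |

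A 5-point gap, about one SD, gives factors of 1.02-1.04.

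**5. Comparison with sampling error.** With 63.75 events, SE(log HR) = 2/√63.75 = 0.250. The 95% interval spans a factor exp(1.96 × 0.250) = 1.63 each way, about 0.28-0.76 around 0.464.

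**6. Power.** 4,000 simulated trials per scenario used 170 per arm, 7 years without dropout and stage not balanced. Overall power, unadjusted against stage-adjusted:
- h = 2: 83.8% vs 84.5% (p = 0.3) and 83.2% vs 83.6% (p = 0.5).
- h = 3: 82.0% vs 84.4% (p = 0.3) and 82.2% vs 83.9% (p = 0.5).

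Across all scenarios, including h = 1.5, the gain was 0 to 2.4 points. Type I error was about 5% for both models. In the subset with more than 8 points' excess in the long-term arm, power at h = 2 was 72-80% unadjusted and 80-87% adjusted. These subsets hold only some 220-300 trials each, so each figure carries an SE of about 2-3 points.

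**The case against.** Which factors to minimize on is a design choice, and any factor left out can differ by chance. Randomization remains valid, type I error is held, and every stated figure reproduces. This stands, and it is why the point is minor.

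The article condenses a fuller protocol, and the SAP, which is not shown, may already adjust for stage. The factor list is also introduced in a way that leaves it formally open. The first part stands: the remark on the analysis concerns only what the article describes. The second has little force. The list closes with institutions and reads as complete, and allocation factors are fixed by the protocol, not by an analysis plan.

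A reader might infer that stage imbalance could explain away the primary result, whether null or positive. The figures do not support this. Moving 0.464 to 1 needs a factor of 1/0.464 = 2.16. At a stage hazard ratio of 2, even all worse-stage men in one arm and none in the other gives only 2. Bringing the upper confidence limit of 0.76 to 1 needs a factor of about 1.32, against 1.08 for a 10-point gap. Only a result already near the significance boundary could be tipped, and a favourable imbalance is as likely as an adverse one. Larger shifts need a stage hazard ratio near 3, for which the article gives no basis.

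**Conclusion.** The point holds as a minor weakness. Stage is the only one of the three eligibility-defining factors not listed for minimization. The article itself treats it as prognostic, and the described primary analysis has no stage term. The consequence is random, not systematic: most imbalances would be smaller than 8 points, and even a 10-point gap shifts the hazard ratio by about 4-8%, well inside its confidence interval. Adjustment mainly protects against the roughly 5-8% of trials with an unlucky excess in the long-term arm, and it helps the credibility of the result.

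This rests on assumed values: 30-50% of men in a single worse stage group and a stage hazard ratio of 1.5-2. The article gives neither, and does not say how T2c and T3a differ in risk.

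**What to change.** Prespecify clinical stage at entry (≤ T2b / T2c / T3a) as a covariate in the Cox model for bPFS, or as a stratum in the log-rank test, alongside the minimization factors. With more than 41 institutions and about 64 events, how institution enters needs its own decision in the SAP. State in advance which analysis is primary, because a stage-adjusted hazard ratio is conditional on stage and is not quite the same quantity as the unadjusted one. If the SAP already does this, no change is needed.

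Cost: one sentence, and two parameters for three stage levels (one if two levels are merged). No patients, visits or data are added, the sample size stays at 170 per arm, and every man is covered, including those already randomized.

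Adding stage to the central minimization is optional. Enrollment had reached 130 of 340 in September 2011, leaving at most 210, and was due to close in September 2012. The change would mean reprogramming a live system and slightly looser balance on the other factors, for no power gain detectable in simulation.

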### Technique of ^125^I-BT

^125^I-BT for all patients is administered using an ultrasound-guided technique with the Mick applicator [15]. The implant is planned to deliver a prescription dose of 110 Gy or more to the clinical target volume (CTV), which includes the prostate gland and treatment margin [16]. Although individual technical aspects are institution-dependent, efforts are made to ensure optimal quality control of the radiation dose. Standardization included training in real-time computer assisted intraoperative technique [17], three types of I-125 activity levels based on prostate volume (< 15 cc; 0.25-0.29 mCi, 15-40 cc; 0.3-0.34 mCi and > 40 cc; 0.35-0.4 mCi), prostate D90 (the mean dose received by 90% of target volume) > 110 Gy, V100 (the mean volume receiving 100% of the prescription dose) > 95%, V150 (the mean volume receiving 150% of the prescription dose) < 60%, urethral V150 (mL) = 0 mL and maximum urethral dose < 220 Gy, rectal V100 (mL) < 0.1 mL. CT images, taken at 2-5 mm intervals, are obtained within 3-7 weeks after ^125^I-BT to determine dose-volume histogram (DVH) for the prostate, urethra, and rectum [16,18]. We organized a quality control committee for this study to assess the variance of postimplant dosimetry. This board will meet regularly while this protocol is running to monitor and compare dosimetry. Although the prescription dose for the I-125 is 110 Gy, the board recognizes that post-implant D90 may vary. One of the goals of the study is not to have local failure result from too low a dose of delivered dose. Therefore, as long as the rectal V100 < 1.0 mL and the urethral D10 (the mean dose received by 10% of target volume) < 200 Gy each center will be allowed to adjust the EBRT total dose if the I-125 D90 < 100 or > 140 Gy. The results of comparative analysis will be reported separately.

